### Data integrity and governance

The institution and collaborators will adhere to Human Biomedical Research Act guidelines to maintain subject confidentiality. All hard copy research documents will be stored in locked cabinets and electronic datasets will be stored in secured end-to-end encrypted platforms (RedCap and OPTIMUM System) where access is solely restricted to investigators. Quality assurance of the study will be conducted by research auditors from an independent collaborative partner, who will review the study-related source data and documentation. The accuracy of the data will be verified by reviewing all study-related documents. Routine monitoring will be conducted to ensure that the study is conducted in compliance with the currently approved study protocol, standard operating procedures and applicable regulatory requirements.

A Trial Steering Committee comprising of the institution leadership (Executive Director of MOHT and Chief Executive Officer of SingHealth Polyclinics) has been established to review the progress of the study implementation and all reported AE and SAE data every six monthly.

### Statistical analysis

Baseline characteristic (e.g. demographics and socioeconomic status, medical history and lifestyle etc.) will be summarised by arm. The Kolmogorov–Smirnov test will be applied to evaluate the normality of data distribution. For continuous variables, mean and standard deviation will be reported if they are normally distributed, otherwise median and interquartile range will be reported. The number of cases and proportions will be reported for categorical variables.

Continuous outcomes, including mean HbA1c, systolic and diastolic blood pressure, BMI, quality of life, medication adherence and rating scales will be compared by arms. Mean difference with 95% confidence interval will be calculated and tested by two sample *t* test if they are normally distributed, and the non-parametric test will be applied otherwise. The number and proportion of patients experiencing a cerebrovascular event will be tabulated by arm. Difference in proportions will be tested using Fisher’s exact test with 95% confidence interval calculated. One interim analysis with the same abovementioned analyses is planned for this trial when all the patients complete month 6’s follow-up visit. The level of significance will be set at 5%. Data will be analysed using Statistical Analysis System v.9.4.

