### Sample size calculation

We assume a clinically significant difference in HbA1c of 0.5% in the sample size calculation based on data published in previous multicentre randomised controlled trials [14, 15]. For a 1:1 allocation ratio and assuming a standard deviation of 1.4 and 1.3 in the intervention and control arms respectively, a sample size of 115 per arm is required to achieve 80% power to detect a difference in HbA1c of 0.5% based on a two-sided 5% significance level. To account for 30% dropout rate over the 24-month follow up, the total sample size was increased to 165 per arm or a total study population of 330 for the RCT. In the subsequent qualitative study, the tentative plan is to interview 30 patients in the intervention group or more until data saturation is reached [16].

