### Outcomes

#### Primary outcome measures

The primary outcome will be the mean HbA1c and magnitude of its change on enrolment and at 6 months in patients in the intervention arm compared with those in the control arm.

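### A normality test decides whether the primary difference in mean HbA1c, the quantity the trial is powered on, is estimated at all

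*Protocol article*

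**What the plan says.** The first paragraph of the Statistical analysis section names one normality check: "The Kolmogorov–Smirnov test will be applied to evaluate the normality of data distribution". It governs the descriptive summaries: "mean and standard deviation will be reported if they are normally distributed, otherwise median and interquartile range will be reported".

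The second paragraph turns to the outcomes: "Continuous outcomes, including mean HbA1c, systolic and diastolic blood pressure, BMI, quality of life, medication adherence and rating scales will be compared by arms". For these the protocol plans an estimated difference in means, with its interval and a *t* test, on one condition: "if they are normally distributed, and the non-parametric test will be applied otherwise". No exception is made for the primary outcome. The non-parametric test is not named, and no effect measure or interval goes with it. The interim analysis, planned once all patients have had the month 6 visit, uses these same methods.

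Under Primary outcome measures the target is a mean: "The primary outcome will be the mean HbA1c and magnitude of its change on enrolment and at 6 months", intervention against control. The Sample size calculation gives 115 per arm, from standard deviations of 1.4 and 1.3, for "80% power to detect a difference in HbA1c of 0.5% based on a two-sided 5% significance level".

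**The concern.** The outcome definition and the sample size both fix the target as a difference in means. The analysis rule then lets the observed distribution decide whether that target is estimated. If the normality test rejects, the protocol promises only a p-value from a rank-type test and, by the descriptive rule, medians with interquartile ranges. On that branch neither the arm means nor their difference with an interval is promised, so nothing can be set against the 0.5% that the protocol calls clinically significant.

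A rank test is also a test of something else. It responds to the whole distribution in each arm, so two arms with equal means but different shapes can differ on it. And because the rule is applied variable by variable, some outcomes and visits could be reported as mean differences and others only as rank-test p-values.

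**Working it through.** **1. The plan's own figure.** Inputs from the Sample size calculation: difference 0.5, SDs 1.4 and 1.3, two-sided 5%, power 80%, 1:1 allocation.

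n per arm = (1.960 + 0.842)² × (1.4² + 1.3²) / 0.5² = 7.849 × 3.65 / 0.25 = 114.6, rounded up to 115. Allowing for 30% dropout: 115 / 0.70 = 164.3, rounded up to 165 per arm, 330 in total. Power at 115 is 80.1% by the normal approximation and 79.8% with the t distribution.

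The stated numbers reproduce, and they do so as a comparison of means. With these inputs the interval at 115 per arm would have a half-width of about 1.96 × √(3.65 / 115) = 0.35 percentage points. That is the result the non-parametric branch would omit.

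**2. How often the normality test rejects.** The protocol gives no skewness for HbA1c, so these are assumed values. Data were simulated from gamma distributions and tested at 5% with the Kolmogorov–Smirnov test corrected for estimated mean and SD (Lilliefors). Rejection of a single sample:

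| Assumed skewness | n = 115 | n = 165 |
|---|---|---|
| 0.5 | about 24% | about 27–30% |
| 0.8 | about 50% | about 69% |
| 1.0 | about 73% | about 88% |

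**3. Dependence on how the test is run.** Suppose instead that each arm is tested separately, values are rounded to 0.1, and the rank test is used if either arm fails. Share of trials leaving the mean-difference branch at 115 per arm:

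| Assumed skewness | Corrected test | Uncorrected test |
|---|---|---|
| 0 (normal) | about 16% | about 0.1% |
| 0.5 | about 53% | about 3% |
| 1.0 | about 97% | about 31% |
| 1.5 | 100% | about 88% |

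The 16% for normal data combines two tests at 5% with the effect of rounding. The protocol does not say whether the test is corrected, or whether it is applied per arm, pooled or to change scores.

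**4. Whether the gate is needed.** At 115 per arm with SDs 1.4 and 1.3 and skewness 1.2 in both arms, separate simulation runs put the size of the Welch t test between 4.4% and 5.2%. Across skewness 0 to 1.5, the 95% interval for the mean difference covers in about 94–96% of runs, with power of about 78–81%. The mean comparison needs no protection at this sample size.

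**5. Whether the two-stage rule harms the test itself.** With the same shape in both arms, the type I error of the gated procedure is about 4–6% and its power at 115 per arm is 80–95%. There is no material inflation and no loss of power.

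**6. Whether the branches answer the same question.** With equal means but different shapes (assumed skewness 1.2 in one arm and 0.2 in the other, 115 per arm), the Mann–Whitney test rejects about 10% of the time and the Welch test about 5%. The branches coincide only when the shapes are alike.

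**The case against.** The best defence is that no inferential damage is shown: size and power of the gated procedure are close to those of the plain t test. That stands for arms of similar shape, and it confines the point to the estimand and its reporting. It is also true that the protocol does not forbid reporting a mean difference alongside a rank test, and that the primary outcome is still named as a mean. The loss of the estimate is therefore a possibility under the rule, not a certainty.

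The rejection rates rest on assumed skewness. This stands too. At mild skewness with an uncorrected test, the switch would be rare.

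An SAP, not available here, might name the rank test. That would not cure the problem, because the conditional rule is stated in the protocol article itself.

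Two stronger readings are tempting and are not supported:

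- A reader might infer that the entry limits (7% to 10% in the inclusion criteria) make non-normality of the primary outcome likely. They restrict HbA1c at entry, not the month 6 value or the change. With a baseline uniform on 7–10 plus a normal change, total SD 1.35 (an assumed model), the corrected test rejects month 6 values about 3–5% of the time, rising to roughly 8–19% after rounding to 0.1. A sample uniform on 7–10 is no stand-in for the outcome: its SD is 3 / √12 = 0.87, against the planned 1.4 and 1.3.
- A reader might infer that a rank test would defeat a cost analysis. Healthcare utilisation from bills is a secondary outcome, but no mean-cost estimate or economic evaluation is planned.

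**Conclusion.** The point holds as a mismatch between a stated analysis rule and the trial's own target. The protocol defines and powers its primary comparison as a difference in mean HbA1c, then makes that difference and its interval conditional on a normality test, with an unnamed test and no estimate on the other branch.

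How often the switch would occur cannot be determined from the protocol. Over the assumed range, at 115 per arm, it runs from almost never (uncorrected test, normal data) to almost always (corrected test, skewness 1.0 or more, both arms tested). Whether the primary estimate is produced thus depends on the data and on an unspecified version of the test, while the t test needs no such safeguard at this size.

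It should not be read as a claim of inflated type I error or lost power. The rule should be changed, but it does not undermine the design or the sample size.

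**What to change.** In the Statistical analysis section, state that the primary analysis is the between-arm difference in mean HbA1c with its 95% confidence interval, by t test (Welch if the variances differ), whatever any normality test shows. Name one rank test, for example the Mann–Whitney test, as a sensitivity analysis only. Preferably report mean differences with intervals in the same way for the other continuous outcomes. Medians and interquartile ranges may still describe skewed variables.

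The cost is about two sentences, best settled before the month 6 analysis. The sample size stays at 115 per arm, 165 after dropout, and no extra data are needed.

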**Methods:**

This mixed-method study comprises an initial randomised controlled trial involving 330 Asian adults with T2DM, aged 26–65 years old with an HbA1c of 7.5–10%, with 115 in the intervention and control arms each. Those in the intervention arm will use standardised Bluetooth-enabled devices to transmit their capillary glucose, blood pressure and weight measurements to the OPTIMUM system. Primary care physicians and nurses will remotely supervise them according to an embedded management algorithm for 6 months, including tele-education via weekly videos over 8 weeks and asynchronous tele-consultation if abnormal or absent parameters are detected. Patients in both arms will be assessed at baseline, 6, 12 and 24 months post-recruitment. The primary outcome will be their HbA1c difference between both arms at baseline and 6 months. Blood pressure and weight control; quality of life, medication adherence, confidence in self-management, diabetic literacy and related distress and healthcare utilisation using validated questionnaires; and incident retinal, renal, cardiac and cerebrovascular complications will be compared between the two arms as secondary outcomes at stipulated time-points. Intervention arm patients will be interviewed using qualitative research methods to understand their experience, acceptance and perceived usefulness of the OPTIMUM system.

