The overarching aim of this mixed-method study is to assess the effectiveness of the OPTIMUM telemonitoring system in improving diabetic management of patients with T2DM by supporting and enhancing their self-management. It includes a randomised control trial (RCT) to compare the glycaemic control, based on the magnitude of HbA1c change at recruitment and at 6th-month post-enrolment, among patients with T2DM in the intervention arm with those in the control arm. The secondary aims include a comparison of blood pressure and weight control; quality of life, medication-adherence, confidence in self-management, diabetic literacy and related distress and healthcare utilisation using validated questionnaires; and incidences of emerging retinal, renal, coronary and cerebrovascular complications of the patients in the two arms at stipulated time-points over 24 months. The study also aims to understand the patients’ experience, acceptance and perceived usefulness of the OPTIMUM system in the intervention arm using qualitative research methods.

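### The primary HbA1c quantity is worded in four ways, and the stated test leaves the baseline value unused; one baseline-adjusted test would settle the wording and gain some power at no cost in patients

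*Protocol article*

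**What the plan says.** The Protocol article describes the primary HbA1c comparison in four places.

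- Primary outcome measures: "The primary outcome will be the mean HbA1c and magnitude of its change on enrolment and at 6 months". This names a level and a change.
- Background, in the paragraph on aims: the glycaemic comparison is "based on the magnitude of HbA1c change at recruitment and at 6th-month post-enrolment". This is the change only.
- Abstract, Methods: "The primary outcome will be their HbA1c difference between both arms at baseline and 6 months". Read literally, this is an arm contrast at each of two visits.
- Statistical analysis: "Continuous outcomes, including mean HbA1c, systolic and diastolic blood pressure, BMI, quality of life, medication adherence and rating scales will be compared by arms". Mean HbA1c is listed and its change is not.

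The Statistical analysis section then fixes the method: "Mean difference with 95% confidence interval will be calculated and tested by two sample" *t* test. The fallback, when normality fails, is a non-parametric test that is not named. Normality is judged by a Kolmogorov-Smirnov test, and the significance level is 5%. The same section plans an analysis once every patient has completed the month-6 visit.

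The Sample size calculation section does not settle the matter. It says "We assume a clinically significant difference in HbA1c of 0.5% in the sample size calculation", with SDs of 1.4 and 1.3, but not whether those SDs belong to the 6-month value or to the change.

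**The concern.** A 6-month mean and a change from baseline are different variables. From the same data they can give different *p* values, and the protocol does not say which one decides. The trial is open-label and the primary data are complete at the month-6 analysis, so a choice made at or after that point could not credibly be called prespecified.

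The second issue is efficiency. The protocol does not merely leave adjustment unmentioned; it states an unadjusted test, with a fallback that is also unadjusted and is selected by a test on the data. Baseline HbA1c is available for everyone and is likely to predict the 6-month value, so some precision is given up for nothing.

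**Working it through.** **Inputs from the Sample size calculation section:** difference 0.5; SDs 1.4 and 1.3; two-sided 5%; 80% power; 115 per arm, raised to 165 for 30% dropout over 24 months. **From Inclusion criteria:** entry HbA1c 7% to 10% (the Abstract says 7.5-10%). **Assumed, because the document gives neither:** the correlation ρ between baseline and 6-month HbA1c (0.2 to 0.7) and the baseline SD (0.7 to 0.87). The SD of 1.35 is taken as that of the 6-month value.

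**1. The plan's own figure.** Average SD = √((1.4² + 1.3²)/2) = 1.351. The normal formula gives n = (1.4² + 1.3²)(1.960 + 0.842)²/0.5² = 114.6, so 115 per arm. Power at 115 is 80.1% by the normal formula and 79.8% by noncentral *t*. Dropout: 115/0.70 = 164.3, so 165. Both stated figures reproduce.

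**2. Three analyses of the same data.** All are members of one family, 6-month value − *b* × baseline. The 6-month *t* test sets *b* = 0 and the change-score *t* test sets *b* = 1. The adjusted model estimates the *b* that minimises the variance, namely ρ × SD(6 months)/SD(baseline). Its residual variance therefore cannot exceed either of the others, apart from one degree of freedom.

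- Adjusted: SD = 1.351 × √(1 − ρ²)
- Change: SD = √(1.351² + SD_b² − 2ρ × 1.351 × SD_b)

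**3. Power at 115 per arm, noncentral *t*.**

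| ρ | 6-month *t* test | Adjusted model | Change *t* test, SD_b 0.7 / 0.8 / 0.87 |
|---|---|---|---|
| 0.2 | 79.8% | 81.4% | 77.4 / 75.4 / 73.8% |
| 0.3 | 79.8% | 83.4% | 81.5 / 80.0 / 78.7% |
| 0.5 | 79.8% | 89.7% | 89.7 / 89.4 / 88.9% |
| 0.7 | 79.8% | 97.5% | 96.7 / 97.2 / 97.4% |

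Over the 6-month *t* test the gain runs from about 2 points (ρ = 0.2) to about 18 points (ρ = 0.7). Over the change test it is about 4-8 points at ρ = 0.2, 2-5 at ρ = 0.3, and under 1 at ρ = 0.5 and 0.7. The last is small because the variance-minimising *b* is then close to 1; for example, 0.5 × 1.351/0.7 = 0.97.

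**4. Type I error, conditional on an either-wins rule.** With no treatment effect, the two test statistics correlate at (1.351² − ρ × 1.351 × SD_b)/(1.351 × SD_change), which is 0.77 to 0.87 over these ranges. If a significant result on either quantity counted as success, the bivariate normal gives an error of 7.3% to 8.0%. If one quantity is named in advance, or both must be significant, it does not exceed 5%.

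**The case against.** **The unadjusted test is not an error.** This stands. It is valid under randomisation, chance baseline imbalance is already covered by its variance, and it matches the sample size calculation. Nor is the trial underpowered on its own inputs. The 30% dropout is allowed over 24 months, so more than 115 per arm may be seen at month 6; with an assumed 140 to 165 per arm, the unadjusted test already has 87% to 92% power.

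**A reader might infer two primary tests at 5% each, and so an inflated type I error.** The document does not support that. No section says that significance on either quantity is enough, and the Primary outcome measures sentence can be read as one outcome reported both as a level and as a change. What the document shows is only that no deciding quantity is named.

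**A reader might also put larger figures on it.** With equal SDs of 1.35 at both visits, the change-score test has only 66% power at ρ = 0.3, and the either-wins error is 8.8% to 9.4%. The entry criterion makes that baseline SD implausible. Values spread evenly over 7-10% have SD 3/√12 = 0.87. The most that the range allows is 1.5, with half the patients at each end, so 1.35 would need nearly everyone close to 7% or 10%.

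**Adjustment is commonly left to a statistical analysis plan.** This is fair as far as silence goes, and one may exist. But the article states an unadjusted test and describes the primary quantity inconsistently, and both of those are on the page.

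**Conclusion.** The point holds as an inconsistency together with an avoidable loss of efficiency. It should be fixed, but it does not threaten the validity of the trial. The four descriptions of the primary quantity disagree whatever is assumed. The adjusted model was at least as powerful as either *t* test in every case computed, but the size of the gain depends on the assumed correlation and baseline spread. It could be small: about 2 points over the 6-month test if the correlation is 0.2, and under 1 point over the change-score test if it is 0.5 or more. The narrow entry range may itself lower the correlation. The 7.3% to 8.0% error rate applies only under a decision rule that the protocol does not state.

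**What to change.** Name one primary quantity: the between-arm difference in HbA1c at 6 months. Test it once, at two-sided 5%, with a linear model of 6-month HbA1c on arm and baseline HbA1c. This replaces both the *t* test and the non-parametric alternative, so the primary method no longer depends on a normality check. The estimated arm effect is identical whether the response is the 6-month value or the change, so the model reconciles the existing descriptions; unadjusted means and changes can still be reported descriptively.

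Use the same sentence in the Abstract, the aims in the Background, Primary outcome measures and Statistical analysis, and fix it before the month-6 analysis. Using the same model for other continuous outcomes that have a baseline value is optional.

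The cost is wording, one model term and one degree of freedom. No further patients, visits or data are needed.

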#### Safety data analyses

The number and proportion of patients experiencing T2DM related complications will be tabulated for each arm with 95% confidence intervals using the exact method. The number and proportion of patients with AE and SAE will be tabulated and compared between both arms.

#### Qualitative data analysis

The initial two to three transcripts will be coded by two investigators with the aid of *NVivo* software to establish a coding frame, before one of them proceeds to complete the coding for the remaining transcripts. The Health Information Technology Acceptance Model will underpin the coding frame. Transcripts will be analysed using the six steps outlined by Braun and Clarke [16]. The emerging themes will be deliberated by the investigators and then finalised prior to manuscript writing for publication.

## Discussion

Appropriate management of T2DM is crucial in mitigating its associated morbidity and mortality. Current models of care of TD2M patients is episodic and often resource intensive. Gaps in monitoring patient between visits exist and continuity of care is key to optimising glycaemic control.

Telemedicine is promising in how care delivery can be modified to improve glycaemic control through continuous monitoring of patients by leveraging on ICT.

The OPTIMUM programme is a novel multicomponent primary care telemedicine programme comprising of remote patient monitoring, education, and timely interventions utilising a bespoke patient-facing smartphone application and clinician-facing web application. The OPTIMUM *VitalHealth* system is culturally adapted through an iterative and collaborative process in close consultation with clinicians, patients and technical staff.

While previous studies have shown a positive impact of telemedicine in the treatment of T2DM patients, baseline characteristics of these patients were largely poorly controlled. Furthermore, these previous studies were done in a Western population which may not be generalizable to an Asian population. We will thus determine the effectiveness and acceptability of a culturally adapted telemedicine in supporting standard of care of T2DM patients.

Findings from this study will enable provide insight into the acceptability of such a model of T2DM and possibly chronic diseases as a whole. It will also better inform policy makers in adopting telemedicine for population health management.

